The recent results of the MANGO study, carried out in Burkina-Faso, showed that the reduction in the dose of RUTF after two weeks of treatment of children suffering from SAM, defined by PT  $< -3$ zscore and / or MUAC  $< 115$  mm and no edema at all, reduced neither weight gain (3.4 g / kg / day; 95% CI -0.4 to 0.4;  $p = 0.92$ ) nor rate of girth gain brachialis (BP), does not affect healing or prolong the duration of treatment (with a median of 56 days; interquartile range [IQR] 35-91) although a small negative effect (0.2 mm / week; 95% CI: 0.04 to 0.4;  $p = 0.015$ ) was observed on linear growth especially for the youngest subjects (24). This study was able to show that children with a reduced dose of RUTF had the same body composition as those who received the standard dose, and came out cured with a fat-free mass almost at the same level as that of healthy children in the community.(25). In terms of energy, reducing the dose

of RUTF leads to a reduction in the daily intake but nevertheless makes it possible to cover the daily energy needs of children treated for uncomplicated SAM.(26).

The MANGO study demonstrates that a reduced dose of RUTF would be as effective as the standard dose in the management of uncomplicated SAM under ideal conditions. It is in this context that we propose to carry out the EfRAMAS project to confirm this in a situation of food insecurity and without additional staff to collect data on children who suffer from SAM in the DRC.

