## **Research hypotheses**

### **Main hypothesis**

Children receiving the reduced dose will have the same weight gain from admission to discharge as children receiving the standard dose of RUTF with a non-inferiority margin of 0.5g / kg / day.

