#### 2.1.4.Results

##### a. Main result

The main outcome of this study will be the velocity of weight gain for each participant in the two study groups (control and intervention group). The acceptable weight gain is 5 g / kg / day for each participant regardless of the group to which he belongs. This weight gain is an average calculated between the gain on admission and on discharge for all the children admitted to the study (intention to treat) and then only for those who are declared cured (per protocol).

To conclude that there is no inferiority, it is assumed that the reduced dose will not be less than the standard dose if the difference in weight gain is less than 0.5 g / kg / day. Therefore, participants in the intervention group should not show a weight gain <4.5 g / kg / day to conclude that the reduced dose of RUTF was not inferior.

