## **2.2. Randomization**

### **2.2.1. Sequence generation**

Randomization by blocks of variable size will be used in this study in each of the 14 UNTAs. In order to ensure that the participants are evenly distributed, in each block there will be the same number of children from each group(41) (42).

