### **2.3.3. Statistical analyzes**

For the quantitative part of the study, the data will be summarized in Mean and Standard Deviation if they are normally distributed (normality test) for continuous variables and in absolute and relative frequencies for categorical variables.

The t-test and the chi-square test will be used respectively to compare the means and the proportions of the socio-demographic characteristics at admission for the quantitative and qualitative variables.

Linear regression analyzes will be used to determine the significant differences between the 2 groups of children for the quantitative variables.

Binary logistic regression analyzes will be used to determine the significant differences between the 2 groups of children for the binomial qualitative variables (2 response modalities).

Multinomial logistic regression analyzes will be used to determine the significant differences between the 2 groups of children for the multinomial qualitative variables (3 or more modalities).

All analyzes will be done in an adjusted and unadjusted model and a difference is statistically significant when the P-value is less than 0.05.

The results will be analyzed using statistical software, in this case STATA, version 17.

The main analyzes will be done by intention to treat (ITT) and per protocol for the main result, in this case, the speed of weight gain. The other secondary results will be analyzed only by intention to treat (ITT).

For the DPM, a score will be assigned to the participant and the sum will constitute the total score for each participant per domain.

For focus group data, after transcription of the recordings into Word 2019, thematic analysis will be done using Excel tables (matrix) or Nvivo® software.

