##### **c.Type of economic evaluation**

This is a parallel economic evaluation of the clinical trial, based on a static decision tree type model simulating the trajectory of all children with SAM included in the trial. SIf the non-inferiority hypothesis is verified in the DRC context, the type of analysis will be a Cost Minimization Analysis, otherwise it will be a Cost Effectiveness Analysis.

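### The protocol's rule for concluding non-inferiority compares no confidence limit with the 0.5 margin and adds an absolute floor of 4.5 g/kg/day, so it does not deliver the one-sided 5% error used to size the trial

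*Protocol*

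**What the plan says.** The main hypothesis (Protocol, Research hypotheses) is equal weight gain "with a non-inferiority margin of 0.5g / kg / day". Section 2.1.4 a turns this into a decision rule: the reduced dose "will not be less than the standard dose if the difference in weight gain is less than 0.5 g / kg / day". It then draws a consequence: "participants in the intervention group should not show a weight gain <4.5 g / kg / day to conclude" non-inferiority. Section 2.1.6 repeats 4.5 g/kg/day as the lowest acceptable average in either group.

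Section 2.1.6 also sizes the trial. It uses a non-inferiority formula with z = 1.64 for alpha and 0.84 for power, a mean of 5 and SD of 2.6 g/kg/day, an expected difference of 0 and a margin of 0.5. The result is 335 per group, raised to 1,000 in total with 20% dropout.

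Section 2.3.3 plans linear regression for quantitative outcomes and says that "a difference is statistically significant when the P-value is less than 0.05". It names the intention-to-treat and per-protocol sets for weight gain, but gives no comparison of an interval with the margin.

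Annex 5, section 3.1 c, makes the economic analysis depend on the verdict: if "the non-inferiority hypothesis is verified in the DRC context, the type of analysis will be a Cost Minimization Analysis"; otherwise a cost-effectiveness analysis is done.

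**The concern.** A non-inferiority conclusion needs the uncertainty of the estimate to be set against the margin. Section 2.1.4 a sets only the difference against it. With no interval or test named, the literal reading is the observed difference. A reduced dose whose true deficit sits exactly on the margin would then pass half the time.

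The floor is a second problem. It replaces a comparison between arms with a fixed number for one arm. The step from 0.5 to 4.5 is valid only if the standard-dose arm gains exactly 5 g/kg/day. The background in section 1.1 gives no assurance of that: the Burkina Faso trial "reduced neither weight gain (3.4 g / kg / day"), the Myanmar programme reports 4 and the Niger programme 9.8. The two parts of the rule can also disagree on the same data, and nothing says which prevails.

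At stake are the trial's confirmatory conclusion about a reduced ration for severely malnourished children, and the type of economic evaluation that follows from it.

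**Working it through.** **Inputs.** SD 2.6, margin 0.5, expected difference 0, alpha 5%, power 80% and 20% dropout are from Protocol section 2.1.6. Equal allocation is from section 2.2.1. The alternative mean gains of 3.4 and 4 are from section 1.1 and serve only as plausible values. A normal approximation is used throughout.

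**1. The plan's own figure.** n = (1.645 + 0.842)² × 2 × 2.6² / 0.5² = 334.4, rounded up to 335 per group. This matches. (The rounded values 1.64 and 0.84 give 332.6.) A one-sided 2.5% level would need 425, so the design error rate is one-sided 5%.

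**2. Standard errors with 400 per arm** (1,000 less 20%, halved). Difference: 2.6 × √(2/400) = 0.184. One arm mean: 2.6/√400 = 0.13. With 335 per arm they are 0.201 and 0.142.

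**3. Difference rule alone.** P(observed deficit < 0.5) = Φ((0.5 − true deficit)/SE), against Φ((0.5 − true deficit)/SE − 1.645) for a one-sided 95% confidence limit. With 400 per arm:

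| True deficit | Rule as written | Confidence-limit rule |
|---|---|---|
| 0 | 99.7% | 86% |
| 0.25 | 91% | 39% |
| 0.5 | 50% | 5% |
| 0.6 | 29% | 1.4% |
| 1.0 | 0.3% | about 0% |

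The 50% in the third row does not depend on sample size.

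**4. Both conditions together, control 5.0 and reduced 4.5.** Let e_r and e_c be the sampling errors of the two arm means, equal in variance and independent. The floor requires e_r ≥ 0 and the difference condition requires e_c < e_r. Together these have probability 3/8 = 37.5%, again at any sample size.

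**5. Floor when the arms are equal but below 5.** P(reduced mean ≥ 4.5) = 1 − Φ((4.5 − mean)/0.13).
- Both arms 4.0: (4.5 − 4.0)/0.13 = 3.85, probability about 0.0001 (0.0002 with 335 per arm).
- Both arms 3.4: (4.5 − 3.4)/0.13 = 8.5, probability effectively 0.
- Both arms 4.5: 50%, although the true difference is 0.

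**6. Under the plan's own assumptions (both arms 5.0).** The difference condition is met 99.7% and the floor 99.99% of the time with 400 per arm (99.4% and 99.98% with 335). Both are met more than 99% of the time.

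**7. Power of a rule that matches the sizing, true difference 0.** One-sided 95% limit: 80% with 335, 86% with 400. Two-sided 95% interval: 70% and 78%.

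**The case against.** The strongest defence is that section 2.1.4 a does not speak of an observed difference, and that section 2.1.6 describes its aim as bounding the true difference, with a proper one-sided formula. On that view margin, alpha and sidedness are all in the protocol, and only the sentence linking a confidence limit to the margin is missing, which a SAP could supply. The sizing is indeed sound. But section 2.1.4 a is not silent: it states a rule, and that rule both omits sampling error and contains the floor. A SAP using a confidence limit would have to depart from it.

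Several stronger readings are not supported:

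- **That non-inferiority is to be concluded from a non-significant P value.** Section 2.3.3 gives a general significance threshold and never ties it to the non-inferiority verdict.
- **That the floor would let through a far worse dose.** With control at 6.0 and reduced at 5.0 the floor alone is met more than 99.9% of the time. If the difference condition must hold too, the pass rate is at most about 0.3% with 400 per arm.
- **That every child must reach 4.5.** Section 2.1.4 a speaks of participants, but section 2.1.6 makes clear that the figure is an average.
- **That wrong verdicts are likely in general.** Under the plan's own assumptions they are not, as step 6 shows.
- **That the 14 randomisation strata are left out of the model.** Section 2.3.3 announces adjusted and unadjusted models without listing covariates. Covariates, strata and the choice of primary model are ordinary SAP content.

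The background rates also run in both directions (3.4 and 4, but also 9.8) and come from other settings. They show that 5 cannot be taken for granted, not that control will fall below it.

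**Conclusion.** The point holds in this form: the decision rule in section 2.1.4 a is wrong as written and does not match the sizing in section 2.1.6. Taken literally, false non-inferiority at a true deficit of 0.5 is 50% under the difference condition. It is about 38% if the floor must also be met and control gains 5.0. The planned rate is 5%. The floor fails an equally effective reduced dose almost surely if both arms gain 4.0.

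These figures rest on SD 2.6, equal arms, normality and the literal reading of the difference as the observed one. The errors arise when the true deficit is near the margin or the control mean is well below 5. With both means near 5 the rule gives the right verdict. The 335 per group is correct and needs no change.

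**What to change.** In section 2.1.4 a, replace the rule with: non-inferiority is concluded if the lower limit of the one-sided 95% (two-sided 90%) confidence interval for the difference in mean weight-gain velocity, reduced minus standard, lies above -0.5 g/kg/day.

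Remove 4.5 g/kg/day as a non-inferiority criterion there, and make section 2.1.6 agree. The figure may stay as a descriptive benchmark.

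In section 2.3.3, add that the P < 0.05 difference test does not decide the primary outcome.

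If a two-sided 95% interval is preferred, restate power as about 70% with 335 and 78% with 400 per arm.

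The cost is protocol wording, submitted as an amendment. It needs no new data and no change to the sample size.

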##### b. Additional results

The additional results expected in this study, in the two groups (control and intervention), are:

- **The duration of the edema melting:** calculated in number of days, this indicator corresponds to the time taken for the lower limbs of SAM children to return to their normal volume. The expected result is the onset of melting of the edemas within the first 14 days after admission and their complete disappearance after 21 days of treatment.
- **The length of stay:** calculated in number of days, this indicator corresponds to the time elapsed between admission and discharge ( $PB \geq 12.5\text{cm}$  and / or  $PT \geq -3$  Z score and / or edema melt). The maximum length of stay is 12 weeks or 3 months(12).
- **The cure rate:** A child will be considered cured if he meets the cure criteria according to his admission category: A  $PT \text{ index} \geq -1.5$  or  $PB \geq 125 \text{ mm}$  during two consecutive visits and no edema during two visits (2 consecutive weeks).
- **The dropout rate:** it is the proportion of children confirmed alive who missed two successive visits. The abandonment is confirmed once after the visit of the RECO which confirms that the child is alive despite his 2 absences during the weekly visits. Children who have abandoned will be followed up to 3 months after the abandonment. For children who can be found, offer the caregivers a small snack at the single appointment 3 months after abandonment to take the anthropometric measurements.
- **Death rate :** the proportion of children randomized to the study who died during the intervention at any time.
- **Cost savings** (average cost saved and cost saved per child treated): this involves comparing the cost of treatment for children in care and declared cured in the two groups. We will use a societal perspective including the direct costs of drugs and RUTF

(purchase, transport, transport and storage) to assess the cost for each child, the HR costs involved in the care, the non-medical costs (food and transport. beneficiaries), indirect costs (loss of productivity).

- The growth velocity of the anthropometric variables and indices: it will be a question of evaluating the prevalence of stunting, underweight of the children included in the study in the two groups at the end of the treatment.

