## **Intervention**

The children admitted to this study will be divided into two groups: control and intervention. For the first two weeks, all children in both groups will receive the same standard dose of RUTF. From the third week, the dose of RUTF will be reduced for the intervention group according to their weight.

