##### **Secondary objectives**

To assess the effectiveness of a reduced dose of RUTF in the management of SAM in terms of:

- **Duration of edema melting** (in days) since admission.
- **Duration of stay** (in days);
- **Performance indicators (cure rate, dropout, mortality, non-respondent, transfer to hospital)**
- **Treatment cost savings** (average cost and total cost per child treated);
- The growth velocity of anthropometric indices
- **Psychomotor development** children
- **Degree of acceptance** a reduced dose of RUTF by healthcare workers and the community
- **Relapse rate** up to 3 months after the “cured” exit from the program.

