### 2.1.2. Participants

#### a. Inclusion criteria

To participate in this study, individuals must meet the following criteria:

- Be between 6 and 59 months old;

- To be MAS: PT <-3 Z-score and / or PB <115mm and / or bilateral edema (+, ++);
- Not having any medical complications;
- Have a good result on the appetite test;
- Live in the selected health zone;
- Consent to participate in the study (informed consent);
- Not have other siblings already admitted to the study. When there are several participants in the same siblings, only the first will be included in the EfRAMAS project. The others will be covered according to the national program but will not be part of the study.

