### 2.1.3.Intervention

As part of the EfRAMAS project, the intervention will consist of the management of SAM with all the care provided for in the national protocol. The only difference will be in the dosage of RUTF over time. Both groups will receive the same dose of RUTF for the first two weeks. Then in the intervention group, the reduction in the dose of RUTF will take place from the third week of treatment (Table 2). The intervention will begin concomitantly in both groups.

Chart 2 : Dose of RUTF per group in number of sachets per week

| Weight (kg) | Standard dose control group |               | Reduced dose intervention group |               |                    |               |
|-------------|-----------------------------|---------------|---------------------------------|---------------|--------------------|---------------|
|             | Admission-Discharge         |               | Weeks 1-2                       |               | Week 3 - discharge |               |
|             | Bags / week                 | Kcal / kg / d | Bags / week                     | Kcal / kg / d | Bags / week        | Kcal / kg / d |
| 3.0-3.4     | 9                           | 168-190       | 9                               | 168-190       | 7                  | 147-167       |
| 3.5 - 4.9   | 11                          | 183-204       | 11                              | 183-204       | 7                  | 102-143       |
| 5.0 - 6.9   | 14                          | 155-214       | 14                              | 155-214       | 7                  | 72-100        |
| 7.0 - 9.9   | 21                          | 144-204       | 21                              | 144-204       | 14                 | 101-143       |
| 10.0 - 14.9 | 28                          | 144-214       | 28                              | 144-214       | 14                 | 67-100        |

When a participant does not respect his date of appointment, the day he presents for the consultation, he will receive the number of sachets in proportion to the number of days remaining before the next appointment.

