|----------------------------------------------------------------------------------------------|----------------------------------------------|------------------------------------------------------------------------------------------------------------------------------------------------------------------------------------------|--------------------------|----------|
|                                                                                              | Position in siblings                         | Position of the child among his biological siblings (at least one parent in common)                                                                                                      | rank                     | ordinal  |
|                                                                                              | Interbreeding interval                       | Number of months separating the child and his unborn child                                                                                                                               | number                   | interval |
| Additional objectives                                                                        |                                              |                                                                                                                                                                                          |                          |          |
| The duration of edema melting (in days) since admission.                                     | Duration of onset of edema melting           | Number of days between the start of treatment and the decrease in volume in the lower limbs                                                                                              | number                   | interval |
|                                                                                              | Duration of total melting of edemas          | Number of days between the start of treatment and the complete disappearance of edema                                                                                                    | number                   | interval |

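### Both arms take the same dose until day 14, so time to onset of oedema melting says nothing about the dose, and time to complete melting from admission is diluted towards no difference

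*Protocol*

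**What the plan says.** - **Dose schedule.** Section 2.1.3 says "Both groups will receive the same dose of RUTF for the first two weeks", and that in the intervention group "the reduction in the dose of RUTF will take place from the third week of treatment". The Executive summary agrees: "For the first two weeks, all children in both groups will receive the same standard dose of RUTF".
- **Objective and time origin.** Section 1.2 lists duration of oedema melting among the secondary objectives, "in days) since admission".
- **Variables.** Annex 8 defines two. Onset is "Number of days between the start of treatment and the decrease in volume in the lower limbs". Total melting is "Number of days between the start of treatment and the complete disappearance of edema".
- **Expected course.** Section 2.1.4 b expects "the onset of melting of the edemas within the first 14 days after admission and their complete disappearance after 21 days" of treatment.
- **Population.** Children with "bilateral edema" graded + or ++ are eligible (section 2.1.2). The protocol does not say how many are expected.
- **Analysis.** Section 2.3.3 plans tests of difference at P < 0.05, with secondary results analysed by intention to treat only. The only non-inferiority margin, 0.5 g/kg/day, is for weight gain.

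**The concern.** The clock starts at admission, but the dose contrast starts two weeks later. An event expected in those two weeks is compared between two groups that are treated identically. An event that can fall on either side of day 14 is compared in a mixture: children who clear early, whom the dose could not affect, and children who clear late, whom it could.

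This matters because oedematous children are a new element here. Section 1.1 describes the earlier Burkina Faso trial as enrolling children without any oedema, whereas this trial admits them. A non-significant oedema result could easily be read as reassurance about the reduced dose in these children, and no margin is set for this outcome to guard against that reading.

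**Working it through.** **1. Overlap of the outcome with the dose contrast (protocol figures only)**

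- Common dose: days 0 to 14. Contrast: week 3 to discharge.
- Onset, expected within 14 days: 0 of 14 days under different doses.
- Complete melting, if it occurs on day 21: (21 − 14)/21 = 7/21 = 33% of the time under different doses. The wording can also mean later than day 21, in which case the share is larger. So 33% is not an upper limit.

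**2. Size of the contrast from week 3 (Chart 2, sachets per week)**

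9 to 7 (−22%), 11 to 7 (−36%), 14 to 7 (−50%), 21 to 14 (−33%), 28 to 14 (−50%). The contrast is substantial, so a child still oedematous at day 14 can show an effect.

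**3. One child**

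Assume the reduced dose multiplies the melting rate by r after day 14. A child who would clear on day T > 14 at standard dose then clears on day 14 + (T − 14)/r.

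- T = 14: day 14 in both arms, whatever r is.
- T = 21, r = 0.8: 14 + 7/0.8 = day 22.8. With r = 0.5: 14 + 7/0.5 = day 28. At weekly visits both are recorded on day 28, against day 21 at standard dose.

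**4. The group mean**

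The protocol gives no clearance curve and no number of oedematous children, so the following are assumptions: exponential clearance, a share q still oedematous at day 21 at standard dose, and 100 oedematous children per arm.

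- Rate λ = −ln(q)/21; mean time (and SD) m = 1/λ; share still oedematous at day 14, s = exp(−14λ).
- Shift in the mean counted from admission: d = s × m × (1/r − 1). Had the doses differed from day 0, it would be m × (1/r − 1). The dilution factor is therefore s.
- Approximate power, two-sided 5%: Φ(d/(m√(2/100)) − 1.96).

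Example, q = 0.10 and r = 0.5: λ = 2.303/21 = 0.110, m = 9.1 days, s = 0.215, d = 0.215 × 9.1 × 1 = 1.96 days. The standard error is 9.12 × √0.02 = 1.29, and the power is Φ(1.96/1.29 − 1.96) = 33%.

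| q at day 21 | s at day 14 | Shift, r = 0.5 (days) | Shift if doses differed from day 0 | Power, r = 0.5 | Shift, r = 0.8 (days) | Power, r = 0.8 |
|---|---|---|---|---|---|---|
| 5% | 14% | 0.95 | 7.0 | 16% | 0.24 | 4% |
| 10% | 22% | 1.96 | 9.1 | 33% | 0.49 | 6% |
| 20% | 34% | 4.46 | 13.1 | 68% | 1.12 | 9% |
| 50% | 63% | 19.1 | 30.3 | 99% | 4.77 | 20% |

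The formula counts one tail, so 4% is no better than chance. It uses the standard-arm SD in both arms and ignores the 12-week limit, the latter mainly affecting the last row. The table shows the direction and rough size of the dilution; it does not predict this trial's power.

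**5. Counting from day 14 instead**

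In the same model, the comparison among children still oedematous at day 14 has about 100s per arm and the undiluted shift. For q = 0.10 and r = 0.5 that is about 21.5 per arm, a shift of 9.1 days and a standard error of 9.12 × √(2/21.5) = 2.78. The standard error in days more than doubles, from 1.29 to 2.78. The ratio of shift to standard error nonetheless rises from 1.96/1.29 = 1.5 to 9.12/2.78 = 3.3.

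**The case against.** The strongest reply is that the intervention is a whole regimen, standard dose for two weeks and then reduced. Counting from admission therefore answers a legitimate question, and it matches the primary outcome, which also runs from admission to discharge. The reply continues that section 2.1.4 b defines the indicator as the time until the limbs regain normal volume. That is complete resolution, the variable that can respond to the dose. Oedema also enters elsewhere: its increase or appearance is a transfer criterion, its absence is part of cure, and its return after discharge is part of relapse. Finally, the protocol does not list oedema among its hypotheses of sameness and nowhere says it will claim equivalence on it.

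Most of this stands, and it limits the point. A reader might infer that the oedema objective must show no difference whatever the reduced dose does, or that only the day-21 visit could reveal one. The documents do not support either. The ration falls by 22% to 50% from week 3, and oedema is checked weekly for up to 12 weeks. A delay could appear at day 21, 28, 35 or later. Nor is slow clearance left unmeasured, since total melting captures it.

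What the reply does not answer is onset, which remains a defined variable with no expected exposure to the contrast, and the dilution of complete melting by children who clear before the doses diverge. The protocol's time origin produces both, and nothing in it corrects for them.

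**Conclusion.** The point holds in a limited form. For children on the expected course, time to onset is uninformative about the dose: 0 of 14 days are under different doses. This rests only on the protocol's own schedule and expectation. Time to complete melting from admission is diluted towards no difference but not forced to it. The dilution factor is the share still oedematous at day 14, which the protocol does not give. Under the assumed exponential curves with 5% to 20% oedematous at day 21, it is 14% to 34%. If half were still oedematous at day 21 it would be 63% and the dilution would be mild.

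It would also go too far to say that equality is built into the objective, or that complete melting is expected by day 21. The text on day 21 is ambiguous, and later clearance means more exposure to the contrast. The supported conclusion is that a non-significant from-admission result would be weak evidence about the reduced dose in oedematous children. Severity is minor, because this is a secondary outcome in a subgroup of unstated size.

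**What to change.** Amend the wording in sections 1.2 and 2.1.4 b and in Annex 8:

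1. Report time to onset of melting by arm descriptively, without a between-arm test.
2. Make the between-arm comparison of complete melting among children still oedematous at the day-14 visit, counting time from that visit. Use the oedema check made before the first reduced ration is handed out. Both arms are treated alike until then, so the dose cannot affect who enters this subset, and the randomised contrast is kept.
3. Keep the from-admission comparison in all oedematous children as supportive.
4. Report by arm the proportion with return or increase of oedema from week 3 to discharge, from the weekly checks in Chart 5.
5. State whether complete disappearance is expected by day 21 or later.

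The cost is wording only: no new data, visits or change to treatment. The downside is a smaller subset of unknown size, so the estimate in days will have a wider confidence interval. That interval should be reported with the result, and a non-significant difference should not be described as equivalence.
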